Building on the notion of embodied cognition, this study proposes that the representation of the mind and emotion of others, i.e., psychological perspective-taking, is grounded in the representation of others’ visuospatial frame, i.e. it is grounded in visuospatial perspective-taking. Indeed, a growing body of evidence supports the close linkage between visuospatial and psychological perspective-taking [70]. For instance, children with autism spectrum disorder exhibit deficits in both visuospatial perspective-taking and empathy (which involves psychological perspective-taking) [71, 72]. Previous research has also found that visuospatial perspective-taking correlates with the personal disposition of empathy and social skills [73–77]. Schurz et al. [78] conducted a meta-analysis of fMRI studies, revealing that overlapping brain regions were involved in visuospatial perspective-taking and theory of mind. In a series of experiments, Erle and Topolinski [62] illustrated that adult participants were more likely to adopt the random thoughts of the target after they were prompted to take the target's visuospatial perspective. Moreover, the results showed that imagining the target's visual frame also increased the perceived similarity and liking for the target. In a recent study, Tian et al. [79] demonstrated a relation between spatial ability and theory of mind in 3.5- to 4-year-olds, and importantly, such relation is mediated by the young children’s visuospatial perspective-taking ability. The authors argued that the psychological mechanism of taking others’ visuospatial perspective may be involved in theory-of-mind development.

If we take the above studies together, we can see that there is strong empirical evidence to argue that simulating the visual world of another person may foster the representation of other's mind and emotional states. As such, scholars have begun to debate the sequence of the development of visuospatial and psychological perspective-taking. And whilst Moll and Kadipasaoglu [80] have argued that understanding the simple mental states of others emerges earlier than visuospatial perspective-taking, there is generally more evidence that suggests otherwise. More scholars regard visuospatial perspective-taking as an essential stepping-stone for the fully developed theory of mind [71, 81, 82].

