### The present study

This proposal draws on the literature of embodied cognition and visuospatial perspective-taking to explore alternative approaches to promote early mind and emotion understanding. The potential role of visuospatial perspective-taking in developing ToM and emotion understanding prompted us to design a visuospatial-based ToM training. The study aims to determine whether training young children’s visuospatial perspective-taking promotes their theory of mind and emotion understanding.

This study involves two training studies to investigate the causal relationship between visuospatial perspective-taking and mental state understanding. In study 1, children aged 4.5 years will be randomly assigned to participate in either (a) altercentric block building (experimental group) or (b) egocentric block building (control group). Experimenters will train children’s visuospatial perspective-taking through a series of block-building activities. Several studies have shown that block building fosters young children’s spatial development [83–85]. The training structure is to reproduce block figures because this task provides abundant age-appropriate experiences for children to grasp the visuospatial relations between objects. It should be noted that this study will specifically train young children to become visuospatial perspective-takers by requiring them to adopt the visual frame of their play partner (i.e., *altercentric block building*). In contrast, children in the control group will be required to reproduce the model figure that looks the same from their own viewpoint (i.e., *egocentric block building*). The partner’s perspectives are irrelevant; subsequently, children’s visuospatial perspective-taking will not be trained. Two research questions will be addressed in study 1: Is children’s visuospatial perspective-taking associated with their ToM and emotion understanding?Do children trained in the visuospatial perspective-taking group improve significantly more than the control children in ToM and emotion understanding after 6 weeks of training?

Previous studies have found that participating in block-building tasks enhances children’s general spatial and mathematics abilities [83, 84, 86, 87]. These two skills will be assessed as a manipulation check to ensure the training improves children’s relevant skills. In this way, any absence of effects will unlikely be attributable to manipulation failure.

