The main goal of study 2 is to determine whether visuospatial perspective-taking or conventional verbal training is more effective in enhancing children’s mind and emotion understandings. ToM training has mostly been heavily language-based because the literature has identified language as a strong correlate of ToM development [42, 44]. Visible social interaction without language input does not promote false-belief understanding. Hence verbal interaction is regarded to be crucial to mind understanding [88]. Moreover, a study by Lohmann and Tomasello [44] involving 3-year-old children also found that training on the theory of mind with minimal linguistic interaction was ineffective in improving children’s false belief understanding. On the basis of the embodiment framework, study 2 will investigate whether simulating the visuospatial experiences of others alone, i.e. *without* the presence of verbal communication, is sufficient to enhance mind and emotion understanding. By doing this, study 2 will compare the training effect caused by visuospatial perspective-taking to the one caused by mere verbal interaction. In study 2, children aged 4.5 years will be randomly assigned to participate in either (a) *socialised altercentric block building* (both visuospatial perspective-taking and verbal interaction), (b) *parallel altercentric block building* (visuospatial perspective-taking only), or (c) *paired dialogic reading* (verbal interaction only). Dialogic reading will be served as a promising interactive approach because this training involves back-and-forth verbal exchanges between children. In addition, dialogic reading is easy to administer with preschool children. The differences between groups in ToM and emotion understanding post-training would indicate whether visuospatial perspective-taking or verbal interaction group will be more effective in fostering mental state understandings. Two research questions will be addressed in study 2:

(1) What is the difference between the effect of visuospatial perspective-taking vs. general verbal interaction training on improving preschoolers’ ToM and emotion understanding?

(2) Do children trained in the socialised altercentric block building group improve significantly more than children in the parallel altercentric block building and paired dialogic reading groups in ToM and emotion understanding after 6 weeks of training?

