**Table Tabb:** 

Training groups	Training activities	Visuospatial perspective-taking	Verbal Interaction
(a) *Socialised altercentric block building* (Fig. 3)	Two children will be seated next to each other, and a toy bear will be seated at 180°, 90°, or 270° angular difference to the line of sight of the children. The experimenter will present a model figure built from blocks. Children will be asked first to reproduce the figure based on their own visual frame. Then, they will be asked to adopt the visual frame of the toy bear and reproduce the figure. Note that the children will be encouraged to discuss the perspective of the toy bear when building the block-figure. Therefore, both visuospatial perspective-taking and verbal interaction will be trained in this group	✓	✓
(b) *Parallel altercentric block building* (Fig. 3)	This training group will have the same procedures as that in the (a) socialised altercentric block building group, except children in this group are required to reproduce the block-figure without discussing the perspective of the figurine. Therefore, only visuospatial perspective-taking will be trained in this group	✓	✗
(c) *Paired dialogic reading*	The storytelling intervention by Ornaghi et al. [101] will be adapted in this training group. The experimenter will read the book series "The Adventures of Jack and Theo" [102] to the children. Children will listen to three stories in each session. After each story, children will be engaged in different language games and conversations. This training will minimize the use of the mental state lexicon to avoid perspective-taking and mentalising. No block-building activity will be involved in the training group. Therefore, only verbal interaction will be trained in this group	✗	✓

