#### Data analysis plan

The preliminary analyses will be the same as those in study 1. Next, repeated measures MANOVAs will be conducted to compare the effectiveness of the three trainings in improving children’s visuospatial perspective-taking, ToM, and emotion understanding abilities. We predict all of the training in study 2 will increase children’s ToM and emotion understanding. In particular, we hypothesise that the *socialised altercentric block building* training will result in the greatest improvement on the children’s ToM and emotion understanding. We expect the paired dialogic reading to enhance children’s general language ability but not their visuospatial perspective-taking ability. In contrast, we expect that the *parallel altercentric block building* will enhance the children’s visuospatial perspective-taking ability but not their general language ability. We further hypothesise that the *socialised altercentric block-building* training will enhance both visuospatial perspective-taking and language abilities because verbal interaction may strengthen children’s developing ability to simulate the visuospatial experience of others. This finding will reveal whether visuospatial perspective-taking is conducive to developing ToM beyond the contribution of verbal interaction.

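### From Study 2 alone, an advantage over dialogic reading cannot be credited to perspective-taking, because block building is present or absent in exactly the same arms

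*Protocol article*

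**What the plan says.** The table under Study 2, Training activities, codes the three arms on two ingredients, visuospatial perspective-taking and verbal interaction:

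- (a) Socialised altercentric block building: "Therefore, both visuospatial perspective-taking and verbal interaction will be trained in this group".
- (b) Parallel altercentric block building: "Therefore, only visuospatial perspective-taking will be trained in this group".
- (c) Paired dialogic reading: "No block-building activity will be involved in the training group". The table concludes that this arm trains verbal interaction alone.

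In arm (a), and in arm (b) because it follows the same procedures, children first copy the model from their own view and then from the toy bear's view.

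Two places state what the comparison is to show. The section The present study says that "study 2 will compare the training effect caused by visuospatial perspective-taking to the one caused by mere verbal interaction", and research question 1 of Study 2 follows from this. The Study 2 data analysis plan closes with: "This finding will reveal whether visuospatial perspective-taking is conducive to developing ToM beyond the contribution of verbal interaction".

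On block building itself, The present study says: "Previous studies have found that participating in block-building tasks enhances" general spatial and mathematics skills in children. The Study 1 data analysis plan relies on the same point. The background section on visuospatial perspective-taking cites a study that "demonstrated a relation between spatial ability and theory of mind in 3.5- to 4-year-olds", and adds that perspective-taking ability mediated this relation.

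**The concern.** The table leaves out a third ingredient, block building, which follows the perspective-taking tick exactly. The stated inference is about a mechanism: what perspective-taking causes, and what it adds to verbal interaction. A contrast that changes perspective-taking and block play together cannot answer that. The protocol does not treat block play as inert, since it expects gains in spatial and mathematics skills from it.

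The answer to Study 2's first research question is at stake, together with the conclusion drawn from it. If the block arms do better than reading, the plan as worded would report a perspective-taking effect, although the same data would fit an effect of block play, or any mixture of the two.

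**Working it through.** **The plan's own figure.** Study 2, Participants, gives a required total of 98 for f = 0.32, alpha 0.05 and power 0.80. For the repeated-measures MANOVA interaction with k = 3 groups and m = 2 time points:

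- s = min(k − 1, m − 1) = 1
- df1 = (k − 1)(m − 1) = 2
- df2 = s(N − k − (m − 1) + s) = 98 − 3 − 1 + 1 = 95
- λ = s·N·f² = 98 × 0.1024 = 10.04

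This gives power 0.804, so 98 is reproduced. It concerns how detectable a difference is, not what the difference is due to, and does not bear on this point.

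**Components by arm.** The inputs are the arm descriptions in the Study 2 training table. Let P be the effect of perspective-taking, V of verbal interaction, B of block building, and m the common gain. Assume for simplicity that effects add.

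| Arm | P | V | B | Mean gain |
|---|---|---|---|---|
| (a) Socialised blocks | 1 | 1 | 1 | m + P + V + B |
| (b) Parallel blocks | 1 | 0 | 1 | m + P + B |
| (c) Dialogic reading | 0 | 1 | 0 | m + V |

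**Contrasts.**

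- (a) − (c) = P + B
- (b) − (c) = P + B − V
- (a) − (b) = V

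The P and B columns are identical. The model has four parameters (m, P, V, B) and the design matrix has rank 3, so only the sum P + B can be estimated. If (a) − (c) is observed to be D, every split with P = D − B fits equally well, from P = D with B = 0 to P = 0 with B = D.

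**Verbal content.** V cancels in (a) − (c) only if it means the same thing in both arms. In (a) the talk is about the bear's viewpoint; in (c) the mental-state lexicon is kept to a minimum. Even P + B is therefore a reading that assumes equal verbal content.

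**Study 1, for comparison.** Both arms build blocks: altercentric is m + P + B, egocentric is m + B, and the difference is P. That separates the two ingredients, but Study 1 has no arm defined by verbal interaction. It also recruits a separate sample, and its perspective target is a play partner, not a toy bear.

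**The case against.** Four points can be made for the plan.

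- **The cited spatial route runs through perspective-taking.** The relation between spatial ability and ToM is reported as mediated by perspective-taking ability, and the protocol credits block building only with spatial and mathematics gains. This stands: the document gives no direct evidence of a block effect on ToM that bypasses perspective-taking. It does not remove the aliasing. The mediation is an observed association, and if ordinary own-view building raised perspective-taking ability, the gain would still not be due to the altercentric instruction.
- **Study 1 already separates the two.** This stands in part. Study 1 can support a claim specific to perspective-taking, but not one about its contribution beyond verbal interaction.
- **A block-free reading arm is intended.** Study 2 asks which training works better, and reading represents conventional language-based training. For that question the comparator is appropriate. Only the mechanistic wording goes further.
- **The spatial analysis is largely planned.** Study 2 uses the Study 1 battery and preliminary analyses, which include repeated-measures ANOVAs of spatial and mathematics skills, and perspective-taking is compared across its three arms. This stands and makes the fix cheap, but these analyses show whether the training changed those skills, not which ingredient changed ToM.

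A reader might also infer that Study 1 put blocks in both arms precisely to remove this confounding, and that Study 2 abandoned the safeguard. The article states no such motive. The purpose it gives for the spatial and mathematics tests is a manipulation check.

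**Conclusion.** The point holds for Study 2 on its own data. Perspective-taking and block building are completely aliased across the three arms, so an advantage of (a) or (b) over (c) cannot be assigned to perspective-taking. The wording in The present study and in the Study 2 data analysis plan claims more than the design can give. Randomisation and the comparison of whole trainings are unaffected.

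The size and direction of any bias are unknown. A reader might infer that the block arms are favoured by a calculable amount, or that false-positive rates are raised by a known factor. The documents do not support that. They give no figure for an effect of block building on ToM, and any rate computed for (b) − (c) would also need a value for V. Setting V to zero would contradict the plan's own prediction that all three trainings, reading included, will raise ToM and emotion understanding. No percentage should be attached.

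A reader might equally infer that perspective-taking can never be credited in this programme. That is also too strong, because Study 1's contrast isolates it from block building. The conclusion rests on the arm descriptions; additivity serves only to write out the contrasts.

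**What to change.** 1. In The present study (including research question 1 of Study 2) and in the Study 2 data analysis plan, state that (a) − (c) and (b) − (c) compare altercentric block building, as a package, with dialogic reading, and do not isolate perspective-taking.
2. Report the three-arm group-by-time result for the 3D Test of Spatial Assembly (TOSA) beside the ToM and emotion results. It would show whether the block arms also differ from reading in general spatial skill. It does not separate the ingredients.
3. Rest any claim specific to perspective-taking on Study 1, and say that Study 1 cannot address a contribution beyond verbal interaction.

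The cost is a narrower Study 2 conclusion. The TOSA is already in the battery and the preliminary analyses, so no new measure, arm or child is needed.

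Adding an own-view building segment to the reading arm is not recommended. Arms (a) and (b) build twice, so block exposure would still be greater in the perspective-taking arms, and the segment would take time from the three stories planned per session.

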**Fig. 3 Fig3:**
[figure not shown]
Socialised Altercentric Block Building Group and Parallel Altercentric Block Building Group

#### Data analysis plan

The preliminary analyses will be the same as those in study 1. Next, repeated measures MANOVAs will be conducted to compare the effectiveness of the three trainings in improving children’s visuospatial perspective-taking, ToM, and emotion understanding abilities. We predict all of the training in study 2 will increase children’s ToM and emotion understanding. In particular, we hypothesise that the *socialised altercentric block building* training will result in the greatest improvement on the children’s ToM and emotion understanding. We expect the paired dialogic reading to enhance children’s general language ability but not their visuospatial perspective-taking ability. In contrast, we expect that the *parallel altercentric block building* will enhance the children’s visuospatial perspective-taking ability but not their general language ability. We further hypothesise that the *socialised altercentric block-building* training will enhance both visuospatial perspective-taking and language abilities because verbal interaction may strengthen children’s developing ability to simulate the visuospatial experience of others. This finding will reveal whether visuospatial perspective-taking is conducive to developing ToM beyond the contribution of verbal interaction.

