#### Data analysis plan

First, we will perform correlation analyses with the pre-test data to examine the associations among visuospatial perspective-taking and ToM and emotion understanding. We hypothesise that there will be positive relationships among preschoolers' visuospatial perspective-taking, ToM, and emotion understanding.

We then will use independent *t*-tests to test the group differences in nonverbal reasoning, inhibitory control, and oral language proficiency and decide if these three variables will be used as covariates in subsequent analysis. Next, we will use repeated measures ANOVAs to examine the post-training improvements in general spatial and mathematics skills in both groups. Previous research has illustrated a positive effect of block-building on preschoolers’ spatial and mathematics skills [83, 84, 86, 87]. We will also examine if the altercentric block-building group improves significantly more than the egocentric block-building group in visuospatial perspective-taking. This will ensure that the altercentric training increases visuospatial perspective-taking that we aim to train.

In the main analysis, we will use repeated measures MANOVAs to determine the post-training changes in understanding mind and emotion across the two groups. We predict that the altercentric block-building group will show greater improvements in ToM and emotion understanding abilities than the egocentric block-building group. Moreover, these improvements will be mediated by the improved visuospatial perspective-taking ability.

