### Study 2: Comparing the roles of visuospatial perspective-taking and verbal interaction in developing theory of mind and emotion understanding

#### Participants

This study will compare the effects of three different training methods on the development of mind and emotion understanding in preschool children. Participants will consist of 120 typically developing Cantonese-speaking 4.5-year-olds (60 males; 60 females), with 40 children in each training group. We used G*Power 3.1 to conduct an a priori power analysis to determine the required sample size. Results indicated that a total sample of 98 participants was required to achieve a power of 0.80 for detecting a medium-to-large effect (*f* = 0.32) at an alpha of 0.05 for a MANOVA (MANOVA: Repeated measures, within-between interaction). To account for a potential attrition rate of 20%, we propose to recruit 40 children per group, thus 120 children in total, via electronic fliers on local internet groups.

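### Study 2 lists the trained skill among the outcomes of its main MANOVAs, and the 0.80 power for the omnibus test does not carry over to the pairwise questions

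*Protocol article*

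**What the plan says.** **Study 2, Data analysis plan.** The preliminary analyses are those of Study 1. Repeated measures MANOVAs then follow, to "compare the effectiveness of the three trainings in improving children’s visuospatial perspective-taking, ToM, and emotion understanding abilities". The socialised arm is predicted to gain most on ToM and emotion understanding. On perspective-taking the section says: "We expect the paired dialogic reading to enhance children’s general language ability but not their visuospatial perspective-taking ability". Both block-building arms are expected to improve it.

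**Study 1, Data analysis plan.** Perspective-taking is tested before the main analysis, with the reason: "This will ensure that the altercentric training increases visuospatial perspective-taking that we aim to train". The main MANOVAs are then used "to determine the post-training changes in understanding mind and emotion across the two groups", so the outcomes there are ToM and emotion understanding.

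**The present study.** The first Study 2 question compares visuospatial with verbal training on ToM and emotion understanding. The second asks whether socialised children "improve significantly more than children in the parallel altercentric block building and paired dialogic reading groups in ToM and emotion understanding".

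**Study 2, Participants.** "a total sample of 98 participants was required to achieve a power of 0.80 for detecting a medium-to-large effect", with f = 0.32, "at an alpha of 0.05 for a MANOVA (MANOVA: Repeated measures, within-between interaction". To allow for 20% attrition, 40 children per arm (120 in all) are recruited.

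**The concern.** There are two separate issues.

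**Outcome set.** The arms are built to differ on perspective-taking: the table of Study 2 training activities marks it as trained in both block arms and not in reading. A group-by-time effect on its measure, the PTT-C, is therefore expected even if ToM and emotion understanding do not move. In a joint model that effect can carry the multivariate test, and a significant result would then answer neither Study 2 question.

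**Power.** The questions are pairwise. The second succeeds only if the socialised arm beats each of the other two. The only power given is for a test of any difference among three arms. A study of this size could pass that test and still be unable to say which training is better.

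**Working it through.** **1. The plan's own figure.** For a repeated measures within-between interaction with k groups and m measurements:

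- s = min(k-1, m-1)
- df1 = (k-1)(m-1)
- df2 = s(N - k - (m-1) + s)
- noncentrality = f² · s · N

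With k = 3, m = 2 (pre and post) and N = 98: s = 1, df1 = 2, df2 = 95, noncentrality = 0.1024 × 98 = 10.04, power 0.804. At N = 97 power is 0.799, so 98 is the minimum. The same setup with k = 2 gives Study 1's 79. For three groups, m = 3, 4 or 6 gives 61, 70 or 85. The 98 is thus a 2-df omnibus test of one outcome measured twice. After 20% attrition, 120 × 0.8 = 96 remain (32 per arm), with power 0.795.

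**2. Joint MANOVA when only perspective-taking moves.** With two time points, the group-by-time test is a one-way MANOVA on gain scores. I simulated it with Pillai's trace at 0.05, 20,000 runs per setting, three outcomes, the same perspective-taking gain in both block arms, no gain in reading, and no ToM or emotion difference. The documents give neither the correlation between gains nor the size of the perspective-taking gain. Both are assumptions, and the ranges below span correlations of 0 to 0.3.

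| Perspective-taking gain (SD) | Significant, 32 per arm |
|---|---|
| 0.5 | about 33-39% |
| 0.64 | about 53-62% |
| 0.8 | about 77-83% |

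With ToM and emotion understanding only, the rate is the nominal 5%.

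**3. Power for the pairwise questions.** f is the SD of the arm means divided by the within-arm SD, here of gain scores. The pattern of means is not stated, so I took two:

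- *Only the socialised arm differs* (d, 0, 0): the SD of the means is d√2/3, so d = 0.32 × 3/√2 = 0.679.
- *Evenly spaced arms, parallel in the middle* (D, D/2, 0): the SD is D/√6, so D = 0.32 × √6 = 0.784 and adjacent arms differ by 0.392.

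A contrast with n per arm and pooled error has noncentrality d√(n/2). At n = 32, √(n/2) = 4 and the error df are 96 - 3 = 93. Each contrast is two-sided at 0.05.

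| Pattern | Contrast | Noncentrality | Power |
|---|---|---|---|
| Only socialised differs | socialised vs either other arm | 2.72 | 0.77 |
| Only socialised differs | both together | – | 0.64 |
| Evenly spaced | socialised vs parallel | 1.57 | 0.34 |
| Evenly spaced | socialised vs reading | 3.14 | 0.87 |
| Evenly spaced | both together | – | 0.33 |

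The 'both together' rows are simulated, because the two contrasts share an arm. With no attrition (40 per arm) they rise to about 0.77 and 0.40. For question 1 (parallel vs reading), power is again 0.34 under even spacing. If only the socialised arm differs, there is no true difference to find. At d = 0.392, 0.80 power would need about 103 per arm.

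**The case against.** **Joint entry is an inference.** The text says MANOVAs, in the plural, and never states that all three outcomes share one model. This stands as a condition on the percentages in step 2. Joint entry remains the natural reading, because Study 1 uses ANOVAs for spatial and mathematics skills and MANOVAs for ToM with emotion understanding. If separate analyses are meant, the outcome-set point becomes a request for clearer wording. The power point is unaffected.

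**The separate check is already there.** A reader might infer that Study 2 has dropped the manipulation check. It has not, since it repeats Study 1's preliminary analyses, which include a perspective-taking comparison. Perspective-taking also carries its own Study 2 hypotheses, so comparing the arms on it is legitimate. What remains in question is its place beside the two target outcomes in the main MANOVAs.

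**No rule makes the omnibus p-value decisive.** The plan states predictions for each construct, so one cannot say that its authors would read a test driven by perspective-taking as a ToM effect. The design permits that result; the documents do not commit to the misreading.

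**Contrasts may be specified elsewhere.** This is a condensed article, and the statistical analysis plan is not at hand. That the article names no contrasts is not an error. Naming them elsewhere would not raise their power, however.

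**The power statement is correct for what it names.** This stands. The 98 reproduces and is labelled as an interaction test. If only the socialised arm differs, a single contrast at 0.77 is close to 0.80. The low figures depend on even spacing. That is plausible, since the plan predicts gains in all three arms, but it is not stated. Splitting alpha between the two socialised contrasts would lower the figures further, but a claim that needs both to succeed does not require it.

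**Conclusion.** The concern holds in two limited parts and should be fixed.

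First, the Study 2 MANOVAs list a trained skill that neither research question concerns and that Study 1 keeps out of its main test. If entry is joint, the test can be significant through perspective-taking alone in about one third to more than four fifths of trials, depending on the assumed gain (0.5 to 0.8 SD) and correlation (0 to 0.3).

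Second, the 0.80 is right for a one-outcome omnibus interaction and does not transfer to the second research question, where power is about 0.33 to 0.64 at 32 per arm, depending on the assumed pattern of means.

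A reader might go further and conclude that the sample size calculation is wrong, or that a positive main test would necessarily be misreported. The documents support neither: the calculation reproduces, and the hypotheses are stated by outcome.

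**What to change.** 1. Restrict the Study 2 main analysis to ToM and emotion understanding. Leave the PTT-C to the preliminary check already carried over from Study 1 and to a separate test of its own hypothesis.
2. Answer the research questions on each outcome with the contrasts that they state: socialised vs parallel, socialised vs reading, and parallel vs reading. Require both socialised contrasts before claiming that the socialised training is best. No alpha split is needed between those two within an outcome. Control multiplicity across the two outcomes.
3. State the contrast power, with the assumed pattern of means, beside the omnibus 0.80.

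The cost is wording and a less favourable stated power, with no new children or data. The change does not raise power. If control across the two outcomes is by a Bonferroni split (0.05/2 = 0.025 per outcome), a single contrast at 32 per arm has power 0.67 at d = 0.68 and 0.24 at d = 0.39, and the plan should say so.
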